### Statistical methods, data collection and management

2.9

#### Statistical methods for primary and secondary outcomes

2.9.1

Data analyses will be performed using R-studio, GraphPad and SPSS. Numerical values will be reported as mean ± SD or confidence intervals. The level of significance is set at 0.05 (two-sided). The Benjamini-Hochberg correction will be used to correct and adjust all *p*-values for multiple comparisons, with the inclusion of a false discovery rate.

The *primary objective* of this study is to investigate the effect of 26 weeks of supplementation with three different dietary fibres (chicory inulin, resistant dextrin, and seaweed polysaccharide) compared to a placebo on working memory (fMRI). Analyses for the primary outcome will compare each fibre group individually to placebo using ANCOVA to adjust for baseline differences, and evaluate the effect of the intervention group at 26 weeks. Specifically, averaged beta weights will be extracted from the regions of interest to determine significant activation at low cognitive load (1-back versus 0-back) and high cognitive load (2-back versus 0-back). *d*-prime values will be calculated to assess working memory task performance. Linear mixed models will be used to evaluate effects on the *secondary and tertiary outcomes* of each dietary fibre individually compared to the placebo at the two different timepoints (baseline and week 26) to measure the interaction group x time. Participants will be set as the random factor, with group and time set as the non-random (fixed) factors. Post-hoc analyses will be performed in case of a significant group x time interaction to understand which fibre(s) specifically differ from the placebo group.

Additionally, *exploratory analyses* will evaluate whether gut- or brain-related biomarkers (e.g., kynurenic acid, serotonin, tryptophan indoles) are associated with cognitive (NTB, MoCA), mood (GDS-15, GAD-7), or physiological outcomes. To elucidate potential mechanisms of the dietary fibre intervention along the MGBA, mediating effects of SCFA levels, TRP metabolite levels and intestinal barrier markers (e.g., LBP, zonulin) between fibre intervention group and cognitive outcomes will be evaluated in case of significant main effects.

In statistical analyses, sex, age, and ApoE genotype will be taken into account as potential modifyers. Furthermore, baseline characteristics such as microbiota composition, habitual fibre intake, risk factor profile and baseline cognitive level may be considered as relevant modifyers determining responsiveness to the dietary fibre intervention.

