### Study aim and objectives

2.1

The aim of the PRECODE study is to evaluate the effect of 26 weeks of inulin, resistant dextrin and seaweed fibres supplementation compared to placebo (maltodextrin) on the MBGA in older adults with SCD+, with the following objectives (Table 1):

*Primary objective*: To determine the effect of 26 weeks of inulin, resistant dextrin and seaweed fibre supplementation on cognitive function by evaluating brain activation during working memory load measured with BOLD fMRI and task performance during 2-back task.*Secondary objectives*: To determine the effects of 26 weeks of inulin, resistant dextrin and seaweed fibre supplementation on (1) cognition as measured by a neuropsychological test battery (NTB) (2) other relevant brain health parameters (3) relevant gut health parameters and (4) immune and metabolic parameters (Table 1)*Tertiary objectives*: To determine the effects 26 weeks of inulin, resistant dextrin and seaweed fibre supplementation on (1) physiological parameters and (2) mood.

**Table 1 tab1:** Objectives and outcome measurements.

Primary objective	Primary outcome measure	
To evaluate the effect of 26 weeks of inulin, resistant dextrin and seaweed fibres supplementation compared to placebo (maltodextrin) on the microbiota-gut-brain axis in older adults with SCD+ on:		
1. Cognitive functioning	i. Brain activation during working memory load measured with BOLD fMRI and ii. task performance during 2-back task	

Secondary objectives	Secondary outcome measures	
To evaluate the effect of 26 weeks of inulin, resistant dextrin and seaweed fibre supplementation compared to placebo (maltodextrin) in older adults with SCD+ on:		
1. Neuropsychological test battery (NTB)	Cognitive functioning as measured by a NTB	CFC scores
2. Other relevant brain health parameters	In plasma/serum	
	Tryptophan metabolites	
	Aβ1-42/Aβ1-40 ratio	
	NfL and GFAP levels	
	Cortisol levels	
	BDNF levels	
	Structural MRI	
	*T*_1_-weighted and FLAIR anatomical images of ROIs	ROIs: Hippocampi, (pre-) frontal, temporal
3. Relevant intestinal health parameters	Faecal microbiota composition	Quantitative ddPCR; Qualitative 16 s rRNA sequencing
	Intestinal barrier integrity	iFABP, sCD14, LBP, LPS, Zonulin
	Intestinal inflammation	Calprotectin, Lipocalin, sIgA, β-defensin
	Gastrointestinal transit time	
	Individual SCFAs and BCFAs	
	Faecal water content and pH	
	GSRS and BSS questionnaires	

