##### Functional magnetic resonance imaging

2.8.1.1

The primary outcome will be evaluated at *T*_0_ and *T*_1_. Working memory function will be assessed using a digit 2-back task during fMRI. Prior studies have demonstrated differential blood BOLD responses in individuals with SCD compared to healthy controls during n-back task performance (117). This validated paradigm consists of three load conditions (0-, 1-, and 2-back), each presented in ten 30-s blocks, with a total task duration of 15 min. A continuous series of single-digit numbers will be shown and participants are instructed to identify whether the current digit matches the one presented (*n*) number of trials earlier. The task includes three working memory load conditions: 0-back (indicated by “–”), in which participants respond when a predefined target digit appears; 1-back (“<−”), in which they respond when the current digit matches the one presented immediately before; and 2-back (“<− −”), requiring detection of matches two positions back in the sequence. Primary outcomes of this study are hence (i) differential BOLD signal responses during the n-back working memory task and (ii) n-back task performance. Analysis of 1-back versus 0-back and 2-back versus 0-back contrasts will identify statistically significant brain activations at low and high cognitive loads, respectively. Main regions of interest include (bilateral) hippocampi, fusiform gyri and dorsolateral prefrontal cortices, based on their previous association with working memory (184, 185). Anatomical MRI scans (*T*_1_-weighted and FLAIR) will be used to assess total/regional grey matter and white matter integrity (hyperintensities via Fazekas scale or automated volumetry), focusing on the hippocampi and (pre)frontal- and temporal cortices as regions of interest.

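### The primary outcome comprises at least 21 tests, and Benjamini-Hochberg is applied to all p-values without a separate primary family, so read literally the bar for a primary claim depends on non-primary results

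*Protocol article*

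**What the plan says.** - **Primary outcome.** Table 1 (section 2.1) gives "Brain activation during working memory load measured with BOLD fMRI and ii. task performance during 2-back task". Section 2.8.1.1 words it as "Primary outcomes of this study are hence (i) differential BOLD signal responses during the n-back working memory task and (ii) n-back task performance".
- **Regions and loads.** Section 2.8.1.1 states: "Main regions of interest include (bilateral) hippocampi, fusiform gyri and dorsolateral prefrontal cortices". Section 2.9.1 extracts averaged beta weights "at low cognitive load (1-back versus 0-back) and high cognitive load (2-back versus 0-back"), and uses d-prime for task performance without naming the load.
- **Comparisons.** "Analyses for the primary outcome will compare each fibre group individually to placebo using ANCOVA". No order among the components and no rule for overall success is given.
- **Multiplicity.** Section 2.9.1 sets a two-sided 0.05 level and adds: "The Benjamini-Hochberg correction will be used to correct and adjust all *p*-values for multiple comparisons". The section heading names both primary and secondary outcomes. The text defines no family and makes no exception for the primary tests.
- **Sample size.** Section 2.5 rests on a single ANCOVA at alpha 0.05 with f = 0.30, and makes no allowance for multiplicity.

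**The concern.** Benjamini-Hochberg controls the expected share of false findings among everything declared significant in the set it is applied to. It does not limit the chance of a false claim in a chosen subset. If the primary tests share a ranking with the gut, metabolite and immune tests, each rejection elsewhere raises the cut-off that a null primary test has to meet. If little else is rejected, the primary tests carry the penalty of a long list of unrelated tests.

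The pool could be long. Section 2.8.3 alone has a 96-marker cytokine panel, or 96 x 3 = 288 fibre comparisons. Some effects are expected: section 2.8.2.4 names bacteria anticipated to change. Whether a fibre is said to have altered working memory could then turn partly on how the stool and blood markers behaved.

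**Working it through.** **1. The plan's own figure.** Noncentral F with lambda = N x f^2, f = 0.30, alpha 0.05, power 0.80, four groups and one covariate gives N = 138 with numerator df 4 (126 with the usual df 3). Then 138/0.85 = 162.4, so 163, or 164 in four equal arms. The stated 138 and 164 are reproduced. Evaluable participants per arm: 138/4 = 34.5. The point below does not depend on this N being right.

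**2. Number of primary tests.** (3 regions x 2 loads + 1 d-prime) x 3 fibres = 7 x 3 = 21. d-prime adds one test per fibre. This is a minimum, because the region list is introduced with a word that leaves it open, and because d-prime at both 1-back and 2-back would give (6 + 2) x 3 = 24.

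**3. When pooling loosens the bar.** With M other tests, of which k are rejected, one further primary test is rejected if p <= 0.05(k + 1)/(21 + M). In a primary-only family the first-step cut-off is 0.05/21 = 0.0024. The pooled cut-off is looser once (k + 1)/(21 + M) > 1/21, that is k > M/21, or about 5% of the other tests. For M = 150, 150/21 = 7.1, so 8 rejections are enough. Below that, the pooled bar is the stricter one.

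**4. Chance of any false primary claim.** All 21 primary tests are null. M = 150 and the responding share are assumptions. A standardised effect d at 34.5 per arm shifts z by d x sqrt(34.5/2): 0.60 x 4.15 = 2.5 and 1.20 x 4.15 = 5.0. Benjamini-Hochberg at 0.05, 6,000 simulated trials per setting:

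| Responding share of the 150 | Effect of responders | Mean cut-off | Primary tests independent | Primary correlation 0.5 |
|---|---|---|---|---|
| 10% | d about 0.6 | 0.0011 | 3% | 2% |
| 30% | d about 0.6 | 0.0054 | 11% | 8% |
| 50% | d about 0.6 | 0.0109 | 21% | 14% |
| 10% | d about 1.2 | 0.0046 | 10% | 7% |
| 30% | d about 1.2 | 0.0136 | 25% | 16% |
| 50% | d about 1.2 | 0.0225 | 39% | 24% |
| Primary tests as their own family | not applicable | 0.0024-0.0026 | 5% | 4% |

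Separate runs differ by one to three points (for example 37-39% for the largest entry and 6-7% for 10% responding at d about 1.2 with correlation 0.5). With 400 other tests and 10% responding, the chance is about 2-3% at d about 0.6 and 7-9% at d about 1.2. The share rejected matters much more than the size of the pool.

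**5. The opposite case.** If nothing else responds, a lone primary effect must clear about 0.05 divided by the number of tests. For d = 0.60 at 34.5 per arm (two-sample t, no gain from the covariate), power is 69% at 0.05 and about 26% at 0.05/21. It is about 11% at 0.05/171 (21 + 150) and 10% at 0.05/189 (39 + 150, hemispheres counted separately).

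**The case against.** **Family definition.** The strongest reply is that the article never says all tiers are ranked in one list. Correcting all p-values is also compatible with correction inside each outcome set, the tiers use different models (ANCOVA, then mixed models), and families are often defined in an analysis plan, which is not shown. This stands in part. A single pool is the literal reading, not a certainty, and under separate families the problem disappears. But the article states a rule covering the primary p-values and exempts none of them, so this is more than detail left for later.

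**Size.** Large figures need responding markers with d about 1.2, twice the primary effect used here, and a high responding share. Nothing in the article predicts that 30-50% of secondary tests respond; section 2.8.2.4 expects change only in selected bacteria. Fibre-specific secondary tests are also run only after a significant interaction, so the make-up of the pool is itself unclear. All of this stands, and it is why the size is given as a range.

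**Readings that go too far.** A reader might infer any of the following; the document does not support them.
- *Gut effects are bound to loosen the primary threshold.* With few rejections elsewhere the bar is stricter.
- *The 1-back BOLD contrasts contradict the objective.* Table 1 ties 2-back to task performance only, and BOLD to working memory load in general.
- *There are 39 primary tests.* That needs the hemispheres analysed separately, (6 x 2 + 1) x 3, which is not stated.
- *A BOLD change in either direction would count as success.* Section 1.3 places hyperactivation early in disease and hypoactivation later, and Figure 2 links the preclinical stage to hyperactivation. They do not treat the two as interchangeable.

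**Conclusion.** The point holds in this form. The primary outcome is at least 21 tests, and the stated multiplicity rule does not separate them from the rest, so taken literally the bar for a primary claim is set partly by non-primary data. The count of 21 and the break-even at about 5% of other tests rejected follow from the text and arithmetic. The error rates (about 2-22% at d about 0.6, about 6-39% at d about 1.2) rest on an assumed 150 other tests, 10-50% responding, and primary correlation of 0 or 0.5. Direction as well as size depends on those assumptions. What does not depend on them is that, under one pool, the chance of a false primary claim has no fixed limit, whereas a separate family of 21 holds it at about 4-6% when all primary tests are null.

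False discovery rate control is a legitimate choice for a mechanistic trial, and the documents do not show that family-wise control is required.

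**What to change.** Before unblinding, amend section 2.9.1 or the analysis plan to say that:
1. the primary tests (listed regions x two loads, plus d-prime, for each fibre against placebo) form their own multiplicity family, adjusted separately from secondary and tertiary outcomes;
2. Benjamini-Hochberg is applied separately within each secondary or tertiary domain;
3. the primary performance measure is the 2-back d-prime, so that section 2.8.1.1 (n-back performance) agrees with Table 1 (2-back performance).

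This needs wording only, with no new data or participants. The cost is that fewer results may be called primary-significant, and the 80% power planned for one test at alpha 0.05 does not carry over to the family. For a lone d = 0.60 effect, power is 69% at 0.05 and about 26% at the first-step cut-off of 0.05/21. Reducing the regions to one summary measure, testing d-prime first, or using Holm or Dunnett within the family would change that trade-off. These are options for the sponsor, not required corrections.

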### Sample size calculation

2.5

To date, most fMRI studies investigating gut interventions have focused on emotional processing (122, 123), with few examining working memory (75, 124). To our best knowledge, no studies have evaluated the effects of dietary fibres in older adults with (or without) cognitive impairment or SCD using fMRI-based n-back tasks. Therefore, sample size was calculated based on the effects on memory performance rather than working memory-related BOLD response. However, at the time of designing the study, no study had evaluated the effects of dietary fibres on working memory performance in SCD, which is why our sample size calculations are based on two different study populations (healthy older adults and MCI patients), as the cognitive level of an SCD population could be considered “in between” these two populations. The effect sizes from one dietary fibre (fermented seaweed) (125) and probiotic study (126) were included in the sample size calculation. The included dietary fibre study in healthy older adults demonstrated effects on cognitive function, including working memory (125), while the probiotic study in older adults with MCI showed improvements in immediate memory, visuospatial and delayed memory (126). The Cohen’s f effect sizes were 0.17 and 0.42, respectively, yielding an average effect size of 0.30. Based on this, a total sample size of *n* = 138 was calculated using G*Power (version 3.1.9.7, Universität Kiel, Germany) for an ANCOVA (*α* = 0.05, power = 80%, 4 groups, baseline as covariate). Allowing for an estimated 15% dropout due to fMRI data quality issues and intervention compliance, the final required sample size is *n* = 164 (41 participants per group).

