##### Randomisation, stratification, allocation concealment, and blinding

2.7.4.1

Individuals eligible for participation will be randomly allocated to one of the four study arms by an independent researcher. Participants will be stratified based on: (i) Sex (male vs. female); (ii) LIBRA cognitive risk factor profile (medium risk: 2–3 points vs. high risk: ≥4 points); (iii) Combined age and education level (≥70 years or low education vs. 60–69 years with high education). High education is defined as *HBO associate degree* (Dutch: HBO; Hoger Beroepsonderwijs).

Study arms will be block randomised within each stratum using SAS (183) to ensure a balanced number of participants per study arm. To preserve blinding, each intervention group will be assigned a unique, randomly generated 4-digit code. A designated staff member, not involved in data analysis, will access group allocations to prepare the intervention materials. Supplements and placebo will be packaged in identical, non-transparent sachets to prevent identification. Breaking the randomisation code of an individual participant will be only be permitted in the case of a suspected unexpected serious adverse reaction, serious adverse event (SAE), or other medical indication as determined by a physician.

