## Initial results

3

By July 2025, baseline measurements were successfully completed. In total, 151 volunteers were randomized into one of four arms and started the intervention. The mean age of our population was 69.4 years (SD = 4.8) and the population consisted of 47.7% females (*n* = 72). The average number of modifiable risk factors was 3.05 (SD = 0.93) and the mean BMI in the population was 27.91 kg/m^2^ (SD = 3.87). Most of the participants (55.6%, *n* = 84) were highly educated, as defined by having at least a 2-year associate degree at a University of Applied Sciences [in Dutch: Hoger Beroeps Onderwijs (HBO)]. Of all subjects, 37.7% carried one or more APOE ε4 allele. The mean MoCA score was 26.09 out of 30 (SD = 2.30) and the average habitual dietary fibre intake was estimated to be 23.68 grams per day (SD = 8.22). Baseline characteristics per intervention arm are presented in Table 6.

**Table 6 tab6:** Baseline characteristics.

		Total	Intervention group			
			A	B	C	D
		*n* = 151	*n* = 37	*n* = 38	*n* = 38	*n* = 38
Sex	% female	47.7	45.9	47.4	50.0	47.4
Education level	% 2-year HBO associate degree or higher	55.6	59.5	44.7	47.4	71.1
APOE genotype	% ε4 carrier	37.7	45.9	39.5	39.5	26.3
Age	mean (sd)	69.4 (4.8)	69.9 (4.7)	69.1 (4.6)	68.5 (4.4)	69.9 (5.6)
Number of risk factors	mean (sd)	3.05 (0.93)	3.03 (0.83)	3.03 (0.85)	3.11 (0.98)	3.03 (1.08)
BMI (kg/m^2^)	mean (sd)	27.91 (3.87)	28.0 (3.88)	28.0 (4.78)	28.2 (3.47)	27.5 (3.30)
Habitual fibre intake (g/day)	mean (sd)	23.68 (8.22)	22.76 (9.29)	23.08 (7.92)	23.91 (6.61)	24.99 (8.94)
MoCA score (max 30)	mean (sd)	26.09 (2.30)	26.16 (2.36)	25.55 (2.81)	26.45 (1.93)	26.18 (2.00)

APOE, Apolipoprotein E; SD, standard deviation; BMI, body mass index; MoCA, Montreal Cognitive Assessment.

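### The primary ANCOVA as described adjusts only for baseline; the stratification factors, and education in particular, should be named as main-effect covariates before unmasking

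*Protocol article*

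**What the plan says.** **Randomisation.** Section 2.7.4.1 states: "Participants will be stratified based on: (i) Sex (male vs. female); (ii) LIBRA cognitive risk factor profile", split at 2–3 versus 4 or more points. The third factor is binary and pools age with education: one level is age 70 or over or low education, the other is age 60–69 with high education. Section 2.2 also lists education among the variables on which randomisation is based.

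**Primary analysis.** Section 2.9.1 compares each fibre with placebo "using ANCOVA to adjust for baseline differences, and evaluate the effect of the intervention group at 26 weeks". The sample-size section (2.5) matches this, with the inputs "power = 80%, 4 groups, baseline as covariate". The outcomes are averaged beta weights from the regions of interest and d-prime.

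**Other variables.** The same section adds that "sex, age, and ApoE genotype will be taken into account as potential modifyers". Risk factor profile and baseline cognitive level are listed as modifiers that may be considered. Neither education nor the combined age/education factor is mentioned in the analysis text.

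**Secondary and tertiary outcomes.** These use a linear mixed model with participant as random factor, group and time as fixed factors, and the group-by-time interaction as the tested term.

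**Observed balance.** Table 6 (section 3) gives the percentage with a "2-year HBO associate degree or higher" as 59.5, 44.7, 47.4 and 71.1 in arms A to D, and 55.6 overall. The arms are not identified.

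**The concern.** Stratified randomisation removes some between-arm variation in the stratifying variables. If the analysis leaves them out, the residual variance still contains what they explain, so the standard error is larger than it needs to be and the test is slightly conservative. The trial has reason to care about precision, since 151 people were randomised against 164 planned.

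The modifier sentence does not close the gap. Asking whether the fibre effect differs by sex, age or genotype is a different question from adjusting the main comparison for those variables, and the text does not say that they enter the primary model as main effects.

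Education has a further problem. Because low education and age 70 or over share one stratum level, perfect balance on the strata still allows education to differ between arms. Table 6 now shows such differences by masked arm. If the covariate set is left open until after unmasking, a decision to adjust for education, or not to, could look driven by the result.

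**Working it through.** **1. The plan's own figure.** Section 2.5 reports "effect sizes were 0.17 and 0.42, respectively, yielding an average effect size of 0.30" and a total of 138. Use noncentral F power with noncentrality λ = N·f², denominator df = N − 4 − q (q covariates) and α = 0.05.
- f = 0.30, q = 1, numerator df 4: N = 138, the stated figure.
- f = 0.30, q = 1, numerator df 3 (the value for four groups): N = 126.
- The stated 138 is therefore reproduced with numerator df 4, which errs on the safe side. This is incidental to the present point.
- Dropout: 138 / 0.85 = 162.4, so 163, or 164 in four equal arms, as stated.

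**2. Precision forgone.** The documents do not say how much residual variance the stratification factors explain beyond baseline. Call it R², assumed 0 to 0.20. Adjustment multiplies the standard error by √(1 − R²), so the effective f becomes 0.30/√(1 − R²). Numerator df is 3. N = 138 is the planned evaluable number, and N = 128 is 151 × 0.85.

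| Assumed R² | √(1 − R²) | Power, N = 138 | Power, N = 128 |
|---|---|---|---|
| baseline only (q = 1) | – | 0.842 | 0.810 |
| 0 | 1.000 | 0.842 | 0.810 |
| 0.05 | 0.975 | 0.862 | 0.831 |
| 0.10 | 0.949 | 0.881 | 0.853 |
| 0.20 | 0.894 | 0.918 | 0.895 |

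The adjusted rows use q = 5: baseline, sex, LIBRA stratum, age and education. Using q = 4 gives the same figures to three decimals. The gain is nil at R² = 0, about 2 points at 0.05, about 4 at 0.10 and about 8 at 0.20. The four extra degrees of freedom take back roughly √((N − 5)/(N − 9)), that is √(133/129) = 1.015 at N = 138, or about 1.5% on the standard error. These powers refer to the four-group test on which the trial was sized.

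**3. Education by arm.** Counts back-calculated from Table 6 are 22/37, 17/38, 18/38 and 27/38, totalling 84/151, which agrees with the text.
- Chi-square across the four arms = 6.76 on 3 df, p = 0.080.
- Permuting education across arms of these sizes, a range at least as wide as B to D occurs about 11% of the time.
- B versus D is the widest of six pairs: 71.05 − 44.74 = 26.3 points.
- The largest gap between placebo and any fibre arm is 14.7 points if placebo is A, 26.3 if B, 23.7 if C and 26.3 if D.

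**4. What such a gap could do.** Suppose education is associated with the outcome by 0.1 to 0.5 residual SD after baseline adjustment (assumed; the documents give no figure). A 26.3-point gap then moves that pairwise difference by 0.263 × 0.1 = 0.03 SD to 0.263 × 0.5 = 0.13 SD. The standard error of a pairwise difference, in residual SD units, is √(2/38) = 0.23 to √(2/32) = 0.25.

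**5. The mixed models.** With two timepoints and complete data, the group-by-time estimate is a difference in mean change. A main effect of a variable that is constant over time adds the same amount at both visits and cancels, so adding sex or education as a main effect leaves that estimate essentially unchanged.

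**The case against.** The strongest reply is that this is a condensed article. A full covariate list may sit in an analysis plan that is not shown, and the text never says that baseline is the only covariate allowed. It is fair that no deliberate exclusion can be inferred. But the article does describe a primary model and a sample-size model, both with baseline as the adjustment, and it gives sex and age a different role. That is a stated model that can be improved, not just a missing detail.

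Three other objections stand and limit the point.

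- **Validity.** A reader might infer that the primary comparison is biased or confounded by education. The documents do not support that. Randomisation keeps the baseline-adjusted comparison valid, and ignoring stratification factors errs on the conservative side.
- **The 44.7% versus 71.1% contrast.** It is the most extreme of six pairs, picked after seeing the data, and the four-arm test does not reject chance. The arms are masked, so B and D may both be fibre arms, a comparison the primary analysis never makes. Adjusting for the baseline outcome also absorbs part of any education effect.
- **Scope.** A reader might extend the remedy to the secondary mixed models or to APOE. The group-by-time term gains essentially nothing with complete data, and APOE was not a stratification factor.

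The size of R² is also unknown, and it may differ between d-prime and the beta weights.

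**Conclusion.** The point holds as a matter of efficiency and pre-specification. The described primary ANCOVA does not carry the factors used to randomise, the modifier sentence does not supply them, and education is missing from the analysis text although it was part of a stratum. The cost is precision: 0 to about 8 power points for an assumed R² of 0 to 0.20, and about 2 points at 0.05. Validity is not at stake.

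The education imbalance is a reason to name education separately, because the combined stratum as randomised would not fully adjust for it. It is not evidence that randomisation failed. The possible shift of 0.03 to 0.13 SD applies only to a pair of arms 26.3 points apart and under the assumed residual association; it is about half a standard error or less.

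**What to change.** Before unmasking, state that the primary ANCOVA, for both the region-of-interest beta weights and d-prime, includes as main effects:
- the baseline value of the outcome;
- sex;
- LIBRA stratum (2–3 versus 4 or more points);
- age and education entered separately, or the combined age/education stratum plus education.

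State also that the interactions with sex, age and ApoE genotype are separate modifier analyses and not part of the primary model. APOE ε4 carriage as a covariate is optional. The group-by-time mixed models need no change on this ground.

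The cost is a sentence or two in the analysis plan and about four degrees of freedom. All the variables are already collected.
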